### **Qualitative Interview Recruitment**

Participants will indicate on the REDCap survey if they are willing to take part in a qualitative interview and will provide contact information for scheduling. Participants will be contacted by the coordinating center research coordinator and invited to take part in the interview. Interviews will be scheduled at a time that is convenient for the participant and will be conducted remotely via phone call or Zoom (HIPAA compliant platform available through Children's Healthcare of Atlanta). The qualitative interviews will be coordinated and conducted by the study coordinating center (Emory/CHOA).

### **15. Withdrawal of Participants**

There are no anticipated circumstances under which participants will be withdrawn from the research without their consent. Participants can choose to stop participating in the study at any time by contacting the research coordinator or PI to sign a "Request for Withdrawal of Authorization".

### **16. Risk to Participants**

This study poses minimal risks to participants. It is possible that participants may become uncomfortable or upset when answering survey items about reproductive health and potential infertility. Similarly, participants may experience emotional discomfort when discussing infertility and/or prior cancer treatment during qualitative interviews. Participants will be able to skip survey questions, take a break during the interview, and stop the survey and/or interview at any time if they become uncomfortable or upset. Contact information for their cancer survivor program will be provided if they have questions or wish to follow-up with a healthcare provider. There is

also a risk for breach of confidentiality for participants. A breach of confidentiality could negatively impact a research participant who would not want their health information, or their participation in a research study, shared with those outside of the research team.

Participating sites should follow institutional guidelines regarding internal study monitoring and/or audits.

### **17. Potential Benefits to Participants**

Participants may not experience a direct benefit from participating in this study. It is possible that participants may benefit from reflecting on their values regarding future fertility through items on the survey or from discussing potential infertility during the interviews. The information gained from the survey and interviews will inform future interventions focused on reproductive health among young female cancer survivors.

#### Importance of the knowledge to be gained

Potential infertility is a source of distress among young adult cancer survivors. Interventions supporting female cancer survivors who are at risk for treatment-related infertility and fertility-related distress are a priority. Knowledge gained from this mixed methods study will inform the testing of a decisional support intervention and may benefit cancer survivors in the future. Results from this study can improve clinical care of cancer survivors through the development of appropriate reproductive health resources and counseling.

### **18. Compensation to Participants**

After completing the quantitative survey, participants will receive a \$10 gift card. Participants who complete the qualitative interview will receive a \$30 gift card. Gift cards will be sent by the coordinating center within approximately one month after completion of the survey and interview (if applicable).

### **19. Data Analysis, Management and Confidentiality**

**Aim 1. Data Analysis:** Statistical analysis will be performed using SAS v.9.4 (Cary, NC) and CRAN R v.3.6 (Vienna, Austria), and statistical significance will be evaluated at the 0.05 threshold. Initial analyses will be undertaken to inspect data for errors, inconsistencies, and incomplete information. Data anomalies and outliers will be examined and corrected or removed if necessary. Descriptive statistics for sociodemographic and developmental factors, and clinical characteristics will be presented as means and standard deviations or medians and interquartile ranges for continuous variables and frequencies/percentages for categorical variables.

The primary outcome of Aim 1 is receipt of an FSA, defined as an answer of 'yes' to the survey item *"Have you ever met with a reproductive specialist to assess your fertility?"*. Based on prior research, and clinical experiences at the participating sites, we anticipate 20% of the sample will report receipt of an FSA.

**Aim 1.1. and Aim 1.2:** Descriptive statistics for reproductive health knowledge, values, health behaviors, and prevalence of reproductive health needs, as well as decisional conflict and fertility-related psychological distress, will be examined using means and standard deviations, medians and interquartile ranges, or percentages and frequencies, as appropriate. For the primary outcome variable (i.e., “yes” for an FSA), frequency and percentage will be calculated with a 95% confidence interval. Hypothesis tests between FSA cohorts (i.e., yes versus no) will be made using two-sample t-tests and chi-square tests of independence (or non-parametric equivalents such as Wilcoxon rank-sum and Fisher’s exact tests); moreover, effect sizes will be calculated to determine standardized differences in exposure values between the FSA cohorts and interpreted using Cohen’s *d* criteria: small (0.2), moderate (0.5), and large (0.8).

**Aim 1.3:** To assess associations between model parameters describing sociodemographic, clinical, reproductive health needs and decisional conflict (covariates) and receipt of an FSA (outcome), we will employ bivariable and multivariable binary logistic regression models. For all logistic regression models, model parameters for sociodemographic, clinical, reproductive health needs and decisional conflict will be treated as fixed effects and study sites will be evaluated as random effects, where appropriate, to account for potential differences in outcome variability between the study locations (i.e., clustering); moreover, fit statistics will be gauged (i.e., AIC, BIC, log-likelihood) for all regressions and appropriate assumptions will be checked, such as linearity in covariates and normality of residuals. Final multivariable results will be guided by the bivariable associations and determined using backward selection procedures, as well as any relevant clinician input. Estimates from these models will be presented as odds ratios for receipt of an FSA with 95% confidence intervals and p-values.

**Power Analysis:** The primary endpoint for this study will be receipt of an FSA. Based on insights from the literature, and our own clinical experiences, we anticipate 20% (n=65) of the sample will have received an FSA and 260 respondents will have not. These sample sizes, which will be obtained by sampling 4 study sites, achieve 80% statistical power to detect an odds ratio of 2.4 for discrete exposures. This odds ratio corresponds to 70.4% of respondents in the FSA group having the exposure, versus 50% of respondents in the non-FSA group having the exposure (i.e., a percent difference of 20.4%). Power was calculated in PASS v.14.0.8 (Kaysville, UT), with a two-sided un-pooled Z-test, an intra-cluster correlation (ICC) of 0.01, and a statistical significance level of 0.05.

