### 3. Background

**Childhood cancer survivor population: characteristics and health risks.** Cancer treatment has improved such that survival rates overall for childhood and adolescent cancer now surpass 80%. There are nearly 400,000 survivors of childhood/adolescent cancers in the United States, most of whom are now young adults and in their reproductive years. Survivors who received gonadotoxic therapies (e.g. alkylating chemotherapy, radiation affecting the gonads, hematopoietic stem cell transplant, and/or surgery impacting the gonads) are at risk for cancer treatment-related infertility. Infertility rates range from 11-26% among young adult female cancer survivors and when compared with healthy siblings, female survivors are more likely to experience infertility and less likely to report a pregnancy. A large proportion of female survivors of childhood cancer receive gonadotoxic treatment – representing a population who may be at risk for a shortened window of fertility – and female cancer survivors may be eligible for fertility preservation options post cancer treatment.

**Cancer survivors overwhelmingly report a desire for children.** Future fertility is a priority among patients and families from the time of cancer diagnosis into long-term survivorship. Across multiple studies of female survivors of childhood cancer, >75% report a desire for children in the future. Fertility preservation options prior to cancer treatment are limited for adolescent females (e.g., oocyte cryopreservation) due to urgency of treatment initiation. Until recently, the only option for prepubertal females – ovarian tissue cryopreservation – was considered experimental. While initiatives are underway to increase access to fertility preservation options at the time of cancer diagnosis, only a small minority of female cancer survivors have cryopreserved oocytes or ovarian tissue. After cancer treatment, potential infertility is a substantial source of distress for young adult cancer survivors and has been associated with depression, anxiety, stress, and trauma. The overall prevalence of fertility-related distress or worry ranges from 20-60% among young adult survivors of cancer and, compared with males, females reported higher distress.

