#### **5. Study Intervention/Design**

This study will utilize an explanatory mixed methods approach to elucidate factors that are related to receipt of an FSA among emerging adult (18-29 years of age) female cancer survivors. Employing a mixed methods approach will allow for a comprehensive exploration of the experiences of young female cancer survivors and their decision to pursue FSA.

Figure 1. Study conceptual model

[figure not shown]

The conceptual model for this study (Figure 1) is informed by the Ottawa Decision Support Framework that purports an individual's decisional needs will affect decision quality, behavior, and emotions regarding the decision. This framework has been used to develop successful decisional aids for fertility preservation at the time of cancer diagnosis, and in this study will guide an assessment of decisional needs for females who have completed cancer treatment. Decisional needs can include an individuals' sociodemographic and clinical characteristics, knowledge and values regarding the decision, and resources to make or carry out the decision. Decisional conflict – a state of uncertainty about an action (e.g., pursuit of an FSA) – is associated with decisions that have uncertain outcomes and potential gains and losses, which can result in delayed decision making. Decisional support interventions address these factors, resulting in an informed and values-based decision. This study will include a comprehensive assessment of decisional needs as they relate to pursuit of an FSA among female cancer survivors; these data will inform the development of a future decisional support intervention.

In this study we propose that sociodemographic and developmental factors, along with cancer clinical characteristics, influence reproductive knowledge, values, and behaviors. These factors inform the individual's values regarding fertility and desire for FSA. In this context, cancer survivors may experience decisional conflict regarding FSA; decisional satisfaction will be explored as an outcome of the decision to pursue/not pursue FSA.

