**Fertility Status Assessment** will be assessed with the item "*Have you ever met with a reproductive specialist to assess your fertility? (e.g. reproductive endocrinologist or a fertility specialist)*". Participants who respond 'Yes' will also be asked details about this assessment (e.g., testing, results, discussion of infertility treatment options). Participants who respond 'No' or 'I don't know' will be asked their level of interest (Likert scale 1 [not at all interested] to 5 [very interested]), and perceived barriers to not receiving an FSA (e.g., lack of awareness, cost).

**Qualitative Interview Data:** Participants for the qualitative interviews will be identified through analysis of the quantitative survey if they (1) indicated on the survey that they are willing to take part in a qualitative interview and (2) responded to the survey item assessing receipt of an FSA. The interviewers for this study are English-speaking, therefore only participants who speak English will be invited to take part in the qualitative interview. We will use a qualitative descriptive approach, which is low-inference and seeks to describe the experiences of participants through their words and

experiences. In line with this approach, we will use maximum variation sampling, which is a preferred method for descriptive qualitative inquiry, to increase the representativeness of the sample in relation to the population being studied by recruiting participants across sites and those who have and have not received an FSA.

Interviews will be conducted until data saturation is reached; we estimate the sample size to be 32 participants, (8 at each participating site). We will try to have approximately equal number of participants who have and have not received FSA at each site, however, some sites may have higher success rates testing patients, therefore stratification of patients by FSA status may not be possible at the site level. However, we will ensure overall there are approximately 16 participants who have received an FSA and 16 who have not received an FSA.

The interview guide will be developed and informed by descriptive results from the quantitative survey. Planned interview questions include a discussion of factors that influenced participants' decision to pursue or not pursue FSA, satisfaction with that decision, barriers encountered when accessing FSA, and resources needed to support survivors who are interested in FSA.

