## **10. Inclusion and Exclusion Criteria**

The population of interest for this study is female survivors of childhood cancer, 18 through 29 years of age.

Inclusion Criteria:

- (1) 18.00 to 29.99 years of age
- (2) diagnosis of cancer < 21.00 years of age
- (3) female sex
- (4) received gonadotoxic cancer treatment (e.g., alkylating chemotherapy agents, heavy metal chemotherapy, radiation including the gonads, cranial radiation  $\geq$  30 Gy, or hematopoietic cell transplant)
- (5) >1 year from completion of cancer treatment

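### The primary outcome is a lifetime 'ever' item with no post-treatment anchor, so a specialist fertility assessment made only before or during cancer treatment may be scored as a survivorship FSA.

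*Protocol*

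**What the plan says.** Section 19 (Aim 1 data analysis) fixes the outcome: "The primary outcome of Aim 1 is receipt of an FSA, defined as an answer of 'yes' to the survey item", followed by the item. Section 6, under the heading on data to be collected, gives the same item, "Have you ever met with a reproductive specialist to assess your fertility", and adds only examples of specialists. Neither place limits the visit to a period.

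Section 6 also says: "Participants who respond 'Yes' will also be asked details about this assessment (e.g., testing, results, discussion of infertility treatment options". Timing is not among the examples given, and no rule uses these details to reclassify a 'yes'. Those who answer 'no' or 'I don't know' receive the interest and barrier items instead.

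The setting is survivorship. Section 5 says the decision framework "in this study will guide an assessment of decisional needs for females who have completed cancer treatment". Section 10 requires ">1 year from completion of cancer treatment". Section 3 describes FSA as recommended for interested survivors at risk of infertility. Section 12 justifies the lower age limit by the legal capacity to make independent decisions such as pursuing an FSA.

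Section 3 also acknowledges fertility care before treatment: "While initiatives are underway to increase access to fertility preservation options at the time of cancer diagnosis", it says, "only a small minority of female cancer survivors have cryopreserved oocytes or ovarian tissue".

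**The concern.** The construct and its measure cover different periods. The construct is a decision made by an adult after gonadotoxic treatment. The measure is any lifetime meeting with a reproductive specialist to assess fertility. An assessment made at diagnosis is a different decision, possibly taken while the participant was a minor, and it cannot show fertility status after treatment.

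This single item drives much of the study:

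- the FSA prevalence, the group comparisons and the Aim 1.3 logistic models;
- the power calculation;
- who contributes a decisional-satisfaction score to Aim 3;
- the interview split of about 16 with and 16 without an FSA;
- who is asked about interest and barriers.

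A survivor assessed only before treatment, and not since, is someone whose interest and barriers the future intervention needs to know. As written she may never be asked. In the models, such respondents dilute associations with survivorship FSA. Factors tied to pre-treatment referral, such as diagnosis or age at diagnosis, could also show associations that have nothing to do with survivorship FSA.

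**Working it through.** **Inputs from the protocol (section 19, power analysis).** 65 with an FSA and 260 without; exposure 70.4% versus 50%; four sites; ICC 0.01; two-sided un-pooled Z-test at 0.05; stated power 80% for an odds ratio of 2.4.

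**Step 1. Reproduce the stated figure.**

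- Odds ratio: (0.704/0.296)/(0.5/0.5) = 2.38, which rounds to 2.4.
- Design effect, 1 + (m − 1) × ICC, with m the group size per site. FSA: m = 65/4 = 16.25, giving 1.1525. Non-FSA: m = 260/4 = 65, giving 1.64.
- SE = √(0.704 × 0.296 × 1.1525/65 + 0.5 × 0.5 × 1.64/260) = √(0.003695 + 0.001577) = 0.0726.
- Power = Φ(0.204/0.0726 − 1.96) = Φ(0.85) = 80.2%.

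The plan's 80% is reproduced, so the sample-size arithmetic is not in question.

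**Step 2. Where pre-treatment answers would sit.** Section 19 gives 20% as the share expected to report receipt of an FSA, which is the expected 'yes' rate on this item. Pre-treatment-only answers therefore form a share f of the 65.

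**Step 3. Outcome left as worded.** Assumptions: f is 10-30% (the documents give no value); pre-treatment-only respondents have the non-FSA exposure rate of 50%; the true post-treatment cases have 70.4%. The observed exposure among 'yes' answers is then (1 − f) × 0.704 + f × 0.5. Power is computed as in step 1, with 65 and 260.

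**Step 4. Outcome restricted to post-treatment assessments.** Same f, with the true odds ratio unchanged. Events are 65 × (1 − f), the rest of the 325 are non-events, and the design effects are recomputed from the new group sizes.

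| f | Pre-treatment only, of 65 | Observed exposure in 'yes' | Observed OR | Power as worded | Post-treatment events (share of 325) | Power, post-treatment outcome |
|---|---|---|---|---|---|---|
| 0% | 0 | 70.4% | 2.38 | 80% | 65 (20%) | 80% |
| 10% | 6.5 | 68.4% | 2.16 | 70% | 58.5 (18%) | 78% |
| 20% | 13 | 66.3% | 1.97 | 59% | 52 (16%) | 75% |
| 30% | 19.5 | 64.3% | 1.80 | 48% | 45.5 (14%) | 71% |

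Worked example at f = 30%, as worded: exposure 0.7 × 0.704 + 0.3 × 0.5 = 0.643; OR = 0.643/0.357 = 1.80; SE = 0.0752; power = Φ(0.143/0.0752 − 1.96) = 48%.

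Restricting the outcome costs events but loses much less power than leaving the mixed group in place.

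**The case against.** The strongest reply is that the problem may be small. The item asks about a meeting to assess fertility, so some respondents whose only visit was for preservation would answer 'no'. Section 3 says that options before treatment were limited for adolescents by urgency, that the only prepubertal option was until recently experimental, and that "only a small minority of female cancer survivors have cryopreserved oocytes or ovarian tissue". Storage is not the same as consultation, but no consultation rate is given and the true share could be near zero. This stands, and it limits the size of the point.

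The survey instrument is said to accompany the protocol but is not in the text available here. The follow-up details are only examples, so timing may already be asked. That also stands. Even so, the outcome as stated does not use timing, and no later analysis plan can recover timing that was never collected.

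A reader might infer more than the documents support:

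- **That every fertility consultation at diagnosis is counted as an FSA.** The item's stated purpose, to assess fertility, rules out a claim that broad.
- **That false cases come on top of the 20%.** If 5-10% of the 260 (13-26 people) were added, prevalence would be 78/325 to 91/325, or 24-28%. But the 20% is already the expected 'yes' rate on this item, so this does not follow.
- **That a factor with no effect would show an odds ratio of about 1.6-2.3.** With 13 added cases all exposed, (45.5 × 130)/(32.5 × 117) = 1.56; with 26, (58.5 × 130)/(32.5 × 104) = 2.25. The arithmetic is right, but it needs the same additive baseline and every misclassified respondent to carry the factor. It is a worst case, not a likely effect.

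It may also be said that this is a minimal-risk, cross-sectional survey meant to inform a later intervention. That bears on the priority of the point, not on whether the definition fits the question.

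**Conclusion.** The point holds as a mismatch between the outcome and the construct. The primary outcome is a bare lifetime 'yes', and the study is about a decision made after treatment. A pre-treatment-only assessment may be counted as an FSA and carried through the Aim 1.3, Aim 3 and interview groups.

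The frequency cannot be derived from the documents. The loss shown, an observed odds ratio of 2.16-1.80 and power of about 70-48% instead of 80%, rests on an assumed 10-30% of the 65 'yes' answers and an assumed 50% exposure rate among those respondents. If the true share is near zero, so is the loss. Spurious associations with referral-related factors are possible, but no likely size can be given.

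The label is cheap improvement: should-fix rather than must-fix.

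**What to change.** Either of two routes would do:

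1. Anchor the item to the period since the respondent completed cancer treatment, and add one item on any specialist visit before or during treatment.
2. Collect the timing of the assessment, or use it if the survey instrument already asks for it, and compare it with the treatment completion date that section 6 already has abstracted from the medical record. This route also suits a survey already in the field.

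Then define the primary outcome as a post-treatment 'yes'. Route the satisfaction, interest and barrier items and the interview groups by that definition, keep the 'ever' version as a sensitivity analysis, and recheck the 20% assumption and the power against the new definition.

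The cost is one survey item and a minor amendment. The downsides are a possibly lower event count (58.5 to 45.5 instead of 65 in the range above) and less comparability with sources that used an 'ever' question.

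### Aim 1.3 selects sociodemographic and clinical factors in one model with decisional conflict, which the protocol places downstream of them, and plans no upstream-only adjusted model

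*Protocol*

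**What the plan says.** Protocol Section 5 describes an ordered conceptual model. It opens with "In this study we propose that sociodemographic and developmental factors, along with cancer clinical characteristics, influence reproductive knowledge, values, and behaviors". It continues with "These factors inform the individual's values regarding fertility and desire for FSA", and then "In this context, cancer survivors may experience decisional conflict regarding FSA". The same section says that decisional conflict can delay a decision.

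Protocol Section 19, Aim 1.3, does not carry that order into the analysis. It states that "we will employ bivariable and multivariable binary logistic regression models", that "model parameters for sociodemographic, clinical, reproductive health needs and decisional conflict will be treated as fixed effects", and that "Final multivariable results will be guided by the bivariable associations and determined using backward selection procedures, as well as any relevant clinician input". On reporting it says: "Estimates from these models will be presented as odds ratios for receipt of an FSA with 95% confidence intervals and p-values". It describes no staged entry of covariate blocks and no multivariable model restricted to upstream factors.

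Aim 3 in the same section uses a parallel covariate list and the same selection approach, with decisional satisfaction as the outcome.

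**The concern.** Aim 1.3 asks which sociodemographic, developmental, psychological, clinical and reproductive health factors are related to receipt of a fertility status assessment (FSA). Suppose a clinical exposure changes decisional conflict, and conflict changes whether the survivor seeks an assessment. A model holding both terms then estimates only the part of the exposure's association that bypasses conflict. Backward selection can go further and remove the exposure, although it is associated with receipt. This would happen even if every covariate had been measured before the FSA.

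The quantitative results are to be combined with the interviews to decide what a decisional support intervention should address. A factor missing from the final model may be read as irrelevant when it in fact identifies who needs support. The bivariable odds ratio still shows the total association, but without adjustment for other upstream factors such as age or insurance. An estimate between the two, adjusted for upstream factors only, is not planned. It would arise only if selection happened to remove the downstream terms.

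**Working it through.** **1. The plan's own power figure.** Inputs from Section 19, Power Analysis: 65 with and 260 without FSA, exposure 70.4% versus 50%, 4 sites, ICC 0.01, two-sided unpooled Z-test at 0.05.

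- Design effects, 1 + (m − 1) × 0.01: with m = 65/4 = 16.25 this is 1.1525; with m = 260/4 = 65 it is 1.64.
- Variance: 0.704 × 0.296/65 × 1.1525 + 0.5 × 0.5/260 × 1.64 = 0.003695 + 0.001577 = 0.005272, so SE = 0.0726.
- Power: Φ(0.204/0.0726 − 1.96) = Φ(0.85) = 80.2%.

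The stated 80% reproduces. It is the power of an unadjusted two-group comparison. Without the ICC the same formula gives 88.5%, which is the comparison for the simulations below, since they have no site clustering.

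**2. Effect of adding a downstream score.** Assumptions, not in the documents: a binary upstream factor with prevalence 50%; a score equal to shift × factor + a standard normal error; and logit P(FSA) = a + 0.6 × score + c × factor. The values of a and c are solved so that N = 325 has 20% FSA and the factor's total odds ratio is 2.4.

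In this model the odds ratio conditional on the score is proportional to exp(−0.6 × shift). Starting from 2.23 at a shift of 0.2 SD:

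- 0.5 SD: 2.23 × exp(−0.18) = 1.86 (1.87 unrounded)
- 0.8 SD: 2.23 × exp(−0.36) = 1.56
- 1.1 SD: 2.23 × exp(−0.54) = 1.30

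| Shift in score | OR in joint model | Retained at 0.05 | Retained at an AIC-type cut (absolute z > 1.41) |
|---|---|---|---|
| 0.2 SD | 2.23 | 79% | 92% |
| 0.5 SD | 1.87 | 56% | 73% |
| 0.8 SD | 1.56 | 27% | 48% |
| 1.1 SD | 1.30 | 13% | 30% |

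Without the downstream term the same factor is significant at 0.05 in about 84-88% of datasets. Shifts of 0.2, 0.5 and 0.8 SD are the small, moderate and large effects of the Cohen's d criteria that Section 19 adopts.

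**3. A second simulation with backward selection actually applied.** Factor prevalence was 0.54, from (0.704 × 65 + 0.5 × 260)/325. The score's log-odds ratio was 0.5, 0.8 or 1.1 per SD, with 2,000 datasets per setting and removal at 0.05.

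| Share of effect through the score | OR in joint model | Retained |
|---|---|---|
| 0% | 2.4-2.5 | 79-84% |
| 25% | 1.9-2.0 | 53-59% |
| 50% | about 1.6 | 27% |
| 75% | 1.25 | 9-11% |
| 100% | 1.0 | 5-7% |

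At a 50% share, about 58% of datasets show the factor significant in the bivariable model and then drop it. The simulation standard error is at most about √(0.5 × 0.5/2000) = 1.1 percentage points.

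**The case against.** A reader might infer that sociodemographic and clinical factors will generally be adjusted away and dropped. The documents do not support that.

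- They give no mediated share. With a small or moderate shift the factor is kept more often than not (79% and 56%). At 0.05, dropping becomes the likelier result only when one factor strongly shifts the score.
- The protocol gives no removal threshold, refers to AIC and BIC, and allows clinician input. An AIC-type cut keeps more factors, as the first table shows.
- Section 5 does not say that upstream factors act only through later ones. Section 3 reports direct obstacles: among survivors without an FSA, 24% cited cost and 22% lack of access. Insurance could work through these without touching decisional conflict.
- The Aim 1.3 covariate list names reproductive health needs and decisional conflict, not knowledge, values or behaviors. Section 5 gives needs no explicit place in its order, so decisional conflict is the only clear intermediate in the list.
- Section 3 also says that having had a fertility evaluation was related to lower decisional conflict. In a cross-sectional survey, conflict may follow the FSA. That is a separate problem of measurement order, and it makes adjusting for conflict more doubtful, not less.
- Bivariable odds ratios are reported, so total associations are not lost from the report. Aim 1.3 asks what is related to receipt, not for causal effects, and a mutually adjusted model is a legitimate exploratory analysis.

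These points limit the size and the wording. They leave one thing standing. Covariate order could be left to an analysis plan, but the protocol itself fixes a joint covariate list and a selection rule that cut across its own conceptual order. It does not say that the resulting estimates are direct associations.

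**Conclusion.** The point holds as a conditional one. Where an upstream factor acts through decisional conflict in the same direction as its direct association, its final-model odds ratio understates its total association and its chance of being retained falls. The fall is modest for a small shift (about 79%, against 84-88% without the downstream term) and large for a large one (27%). These figures assume a total odds ratio of 2.4, a score log-odds ratio of 0.6 per SD, one upstream and one downstream term, no site clustering and removal at 0.05. None of these mediation inputs comes from the protocol.

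The firm part needs no simulation: no planned model is designed to give upstream associations adjusted only for other upstream factors, and the final model's estimates are not identified as direct associations.

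**What to change.** In Section 19, Aim 1.3:

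1. Add a multivariable model with sociodemographic, developmental and clinical factors only, and report the upstream odds ratios from it.
2. Then report the model that adds reproductive health needs and decisional conflict, and label its upstream estimates as direct associations.
3. State that no upstream factor is removed from the reported results because of a downstream term.

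Use the same order for Aim 3. The cost is a change of wording and one or two more table columns. No new data are needed.
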